### STEMI Identification with 12-Lead PHECG

• Proportion of STEMI subjects within the target door-to-reperfusion times comparing basic vs. advanced life support paramedics.

• Paramedics and computer software interpretation of the 3-lead and 12-lead PHECG of all STEMI subjects will be compared with a gold standard (defined as consensus between two investigators' independent interpretation blinded to paramedic or software interpretation)

### Access to Interventions

The rate of reperfusion strategy utilization across groups including fibrinolysis, percutaneous coronary angiography and intervention, coronary artery bypass surgery, bypass to PCI centre directly vs. transfer from a non PCI centre.

### Economic Outcomes

• The direct costs of the 12 lead PHECG program will be estimated.

• Impact on life expectancy gains through reductions in mortality based on the age and gender of subjects [33-35];

• Cost savings with survival benefits for the dominant treatment strategy or cost and outcome trade-offs if one treatment strategy demonstrates cost increasing with survival benefits

• Incremental cost-effectiveness, as measured through additional cost per reduction in door-to-reperfusion time and additional cost per life year gained, will be calculated [36,37].

### Patients Enrolment

A single trained data guardian/abstractor at each base hospital will screen all ambulance call reports and identify all eligible cases. Trained inhospital data abstractors will be notified to conduct a chart review at each receiving hospital.

### Data Management

All prehospital and inhospital data will be abstracted by trained staff and entered on a web based interface employing a structured data set (Additional file 1 - Prehospital Data Variables and Additional file 2 - Inhospital Data Variables) that complies with institutional, privacy and ethical requirements. A manual of operations defines the data name, definition and abstraction instruction for each variable. Error and logic checks were built into the database to screen for abnormal values across forms and within forms at point of entry.

### Analysis Plan

The primary outcome, and treatment time intervals, will be analyzed with one-way ANOVA and subsequent pair-wise multiple comparison procedures across the four treatment strategies. Different covariates (Table 3) will be analyzed using multiple linear regressions and they will be introduced into the model and evaluated as potential confounders. Variables will be retained if they have had an effect of 5% or greater on the coefficients for door-to-reperfusion time. Survival at 30 days and one year for STEMI patients will be analyzed as a binary outcome (Chi square) and as a survival analysis. Covariates that may affect survival will be analyzed with a Cox PH Regression Model. Adverse event rates will be analyzed with a Chi square analysis or a Fisher's exact test.

**Table 3 T3:** Analysis Plan - List of Covariates

1. Presence of cardiac catheterization lab in the primary destination hospital with the ability to perform 24-7 emergent primary angioplasty;
2. Fully affiliated teaching hospital;
3. Is the ED on Time Consideration (TC) or deferral from ambulances based on workload of acutely ill or injured patients?
4. Is the ED on Consideration (C) or deferral from ambulances based on workload?
5. Weekday;
6. Weekend;
7. Time of day in 8 hour intervals (08:00-16:00, 16:00-24:00, 24:00-08:00);
8. Age (as a continuous variable);
9. Sex;
10. History of MI;
11. History of CABG;
12. History of angioplasty;
13. Location of STEMI (anterior, posterior, inferior);
14. Off load delay (minutes);
15. PCA or PCI or bypass surgery.

Economic outcomes will be analyzed using decision analysis supplemented with probabilistic sensitivity analysis in a simulation model. Direct costs will be estimated for each of the four treatment strategies. Door-to-reperfusion times and mortality will be available at the patient level, which will allow for the calculation of averages as well as variability estimates for analysis of uncertainty. Average cost and effectiveness (time-to-reperfusion interval and life years) will be calculated and if one treatment strategy is found to be superior (i.e. cost savings with survival benefits), and then these results will be reported in a cost consequence format. If the superior strategy is found to involve cost and outcome trade-offs (i.e. cost increasing with survival benefits), then incremental cost-effectiveness, as measured through additional cost per reduction in time-to-reperfusion interval and additional cost per life year gained, will be calculated.

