## Methods/Design

### Study Design

PREDICT is a prospective, population-based cohort study of four patient care strategies provided by regional EMS services to patients with chest pain and suspected ischemia.

1. 3-lead PHECG and transported to the nearest receiving ED who were not eligible for bypass based on transport time.

2. 3-lead PHECG and transported to the nearest receiving ED who were eligible for bypass based on transport time, if 12 lead PHECG was possible.

3. 12-lead PHECG and prehospital notification transported to the nearest receiving ED who were not eligible for bypass to a PCI center based on transport time.

4. 12-lead PHECG with prehospital notification and eligible for bypassing the nearest receiving ED with transport to a PCI center.

Bypass eligibility was based on transport distance of patients from their pick-up location to PCI center and the cut-off point was 60 kilometres.

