### Study Outcomes

#### Primary Outcome

The primary outcome of this study is to compare the proportion of study subjects who receive reperfusion within the target door-to-reperfusion times across the four care strategies. Target door to reperfusion times are 90 minutes for primary PCI intervention (door-to-balloon time) and 30 minutes for fibrinolysis (door-to-needle time)[30-32].

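### The only covariate adjustment stated for the yes/no primary outcome is linear regression, with confounders chosen by their effect on door-to-reperfusion time

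*Protocol article*

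**What the plan says.** The Primary Outcome section sets the aim as to "compare the proportion of study subjects who receive reperfusion within the target door-to-reperfusion times across the four care strategies". Two cut-offs define success: "Target door to reperfusion times are 90 minutes for primary PCI intervention (door-to-balloon time) and 30 minutes for fibrinolysis (door-to-needle time". The result for each patient is therefore yes or no. The Sample Size Calculation section agrees, since Table 2 lists baseline and intervention percentages with odds ratios.

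The Analysis Plan groups this outcome with the continuous time intervals: "The primary outcome, and treatment time intervals, will be analyzed with one-way ANOVA", followed by pairwise comparisons among the four strategies. On adjustment it says: "Different covariates (Table 3) will be analyzed using multiple linear regressions and they will be introduced into the model and evaluated as potential confounders". The retention rule is: "Variables will be retained if they have had an effect of 5% or greater on the coefficients for door-to-reperfusion time".

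The same section does assign binary methods elsewhere: "Survival at 30 days and one year for STEMI patients will be analyzed as a binary outcome (Chi square) and as a survival analysis". It names chi-square or Fisher's exact test for adverse events and a Cox model for covariates of survival. It names no binary regression for the within-target proportion.

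**The concern.** Study Design states that "PREDICT is a prospective, population-based cohort study of four patient care strategies". Which strategy a patient receives depends on the local EMS service and on distance to a PCI centre, so a crude comparison of the four groups is open to confounding. The adjusted comparison should carry the conclusion.

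As written, that adjustment appears to be built on minutes to reperfusion. A model of mean minutes answers a different question from the share of patients treated within target. It differs in scale, because the two targets are 60 minutes apart, and in population, because a patient who is never reperfused has no time to model. At stake is whether the primary question gets a confounder-adjusted answer at all, and whether the covariates in that answer were chosen for the right outcome.

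**Working it through.** **1. The sample size treats the outcome as binary.** Inputs from the Sample Size Calculation section: baseline 37.4%, alpha 0.05, power 80%. The two-sided pooled formula is n = [1.96·√(2p̄q̄) + 0.8416·√(p₁q₁ + p₂q₂)]² / d², with continuity correction n′ = (n/4)·[1 + √(1 + 4/(n·d))]².

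For 37.4% against 47.4%: p̄ = 0.424 and d = 0.10. Then n = (1.3698 + 0.5852)² / 0.01 = 382.2, and n′ = (382.2/4)·(1 + √1.1047)² = 402.0.

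| Comparison | Stated n per arm | Recomputed n′ | Stated OR | Recomputed OR |
|---|---|---|---|---|
| 37.4% vs 47.4% | 402 | 402 | 1.5 | 1.51 |
| 37.4% vs 52.4% | 185 | 185 | 1.8 | 1.84 |
| 37.4% vs 57.4% | 106 | 107 | 2.3 | 2.26 |

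Table 2 is a two-proportion calculation, reproduced to within one patient.

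**2. Crude ANOVA on 0/1 data.** Simulation with 100 per group (the recruitment goal) and 100,000 replicates:

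| True proportions (%) | ANOVA rejects | Chi-square rejects | Decisions differ |
|---|---|---|---|
| 37.4 / 37.4 / 37.4 / 37.4 | 0.052 | 0.051 | 0.06% |
| 37.4 / 37.4 / 47.4 / 57.4 | 0.813 | 0.812 | 0.08% |

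The crude test is sound enough.

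**3. Two targets on one scale.** Only the document's cut-offs are needed. A PCI patient at 80 minutes succeeds (80 < 90). A fibrinolysis patient at 40 minutes fails (40 > 30). A model of minutes ranks the second patient 40 minutes better. Strategy 4 goes to a PCI centre and strategies 1 to 3 to the nearest ED, so the treatment mix can be expected to differ by strategy; Access to Interventions plans to measure it. Table 3 has a covariate for angiography, PCI or bypass surgery, which could absorb part of a shift in means. But it records care given after the strategy took effect, and the modelled outcome is still minutes.

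**4. A mean is not a proportion (assumed values).** Take log-normal times and the 90-minute target. The median is mean·exp(−s²/2), and P(<90) = Φ[ln(90/median)/s].
- Group X, mean 100, s = 0.8: median 72.6, P = Φ(0.268) = 60.6%.
- Group Y, mean 95, s = 0.3: median 90.8, P = Φ(−0.030) = 48.8%.

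The mean favours Y by 5 minutes; the proportion favours X by about 12 points.

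**5. Different populations (assumed values).** Suppose 25% of one group and 10% of another are never reperfused, and half of those reperfused are within target in both. Over all STEMI subjects the proportions are 0.75 × 0.50 = 37.5% and 0.90 × 0.50 = 45.0%. If the reperfused have the same times in both groups, a regression of minutes sees no difference.

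**The case against.** The covariate sentence names no dependent variable and comes straight after a sentence whose first subject is the primary outcome. It could mean a linear model on the 0/1 outcome, which is a legitimate risk-difference model. Door-to-reperfusion time in the retention rule could be loose shorthand for the outcome. A reader might infer that the primary endpoint never gets an adjusted analysis; the document does not establish that. It supports only that no adjusted model is clearly stated for the endpoint. The retention rule still stands against the plan on either reading, because taken at its word it selects confounders on time.

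A reader might also infer that ANOVA on a binary outcome is invalid here. Step 2 shows otherwise.

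The examples in steps 4 and 5 are weak as evidence of magnitude. At 100 per group, step 4 implies SDs of about 95 and 29 minutes, so the 5-minute difference has a standard error of √(95² + 29²)/10 ≈ 9.9 (z ≈ 0.5), and the 12-point difference has z ≈ 1.7. In step 5, z ≈ 1.1, and 7.5 points is smaller than any effect in Table 2. The unequal spreads in step 4 have no support in the document. All of this is fair: the examples show that a disagreement can occur, not that it would be large or detectable in this study.

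Step 5 also counts the never-reperfused as not within target. That is the natural reading, but the Primary Outcome section does not say so. Steps 3 and 4 do not depend on it.

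Finally, an article may leave model details to a fuller plan. The absence of the word logistic would be no finding. The point here is a stated method and a stated selection rule that do not fit the stated endpoint.

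**Conclusion.** The point holds as a mismatch between endpoint and adjustment. The outcome is defined and sized as a proportion, while the only adjustment given for it is linear regression with confounders kept by their effect on door-to-reperfusion time. On the natural reading, the adjusted result concerns mean minutes among reperfused patients and can rank strategies differently from the primary outcome. On the more generous reading, the model is acceptable but its covariates are chosen on another outcome.

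The conclusion rests on the wording of the Analysis Plan and on the two targets. The size of the distortion cannot be derived from the document, because it gives no time distributions, treatment mix by strategy or rate of non-reperfusion. No claim is made that the crude test is wrong or that a reversal is likely.

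**What to change.** In the Analysis Plan:

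- State an adjusted binary model for within-target reperfusion, with strategy as a four-level factor: logistic regression, or modified Poisson or binomial regression if risk differences are wanted.
- Apply the 5% change-in-estimate rule to the strategy coefficients of that model.
- State that the denominator is all STEMI subjects, with those never reperfused counted as not within target.
- Keep the linear models of time for the secondary time intervals only.

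Two further changes are optional: a four-group chi-square test in place of the crude ANOVA for the primary outcome, and log-scale or time-to-event analysis of the intervals.

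The cost is wording in the analysis plan and slightly more analysis work. The data and the sample size stay the same, since Table 2 is already a calculation for proportions.

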### Sample Size Calculation

The recruitment goal is to enrol 100 STEMI prospective subjects per group (e.g. as in the WEST trial)[28], for a total of 400 STEMI subjects. The primary estimate is based on a difference in the proportion of patients who received reperfusion (fibrinolysis or PCI) within target door-to-intervention times. We based our calculation using estimates from Canto et al., 2002[29]. In that study there was an increase in the percentage of the patients who received lytic therapy within 30 minutes, from 31% to 50% (an absolute difference of 19%). The percentage of patients who received PCI within 90 minutes increased from 29% to 48% (an absolute difference of 19%). Furthermore there was a combined 24% higher odds of receiving fibrinolytic therapy or PCI with the active EMS involvement (odds ratio 1.24, 95% CI 1.21 to 1.28, p < 0.001). Calculations were conducted using PASS software, assuming an alpha (α) of 0.05 and power of 80% (Table 2).

**Table 2 T2:** Sample size calculation for the PREDICT study

Baseline %	Intervention %	Absolute Difference	Odds Ratio	Number per arm
37.4	47.4	10%	1.5	402

37.4	52.4	15%	1.8	185

37.4	57.4	20%	2.3	106

To estimate the number of potential subjects that could be enrolled in the study, the annual rate of STEMIs that would occur within a 60 minute transport time of the closest PCI centre was determined. The surrounding areas within 60 minutes of a PCI centre were first identified using data from a Cardiac Care Network of Ontario (CCN) report published in 2004[6]. Current population estimates were then assigned to each of the surrounding areas using population estimates for 2006[27]. For counties or regions where a proportion of the population resided outside a 60 minute radius, population data from the 2006 Canadian census was used from the census subdivisions to adjust the 2006 population estimates[27]. To determine the rate of STEMI, an estimate of 571 per 1,000,000 inhabitants was calculated by taking an estimate obtained using CIHI data of 6524 STEMIs in Ontario for fiscal 2001/02 and dividing it by the 2006 Ontario Census Population and determining the rate per million inhabitants[6,27]. The number of potential subjects to be entered in per year was then estimated by assuming a 50% transport by EMS rate and a potential recruitment rate of 70%.

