### Treatment Time Intervals

• Prehospital scene time interval defined as time from arrival at scene to departure from scene;

• Transport time interval defined as time from departure from scene to arrival at destination hospital;

• Symptom onset time interval defined as time from symptom onset reported by subject to reperfusion intervention (defined as time to drug administration or balloon inflation);

• Primary hospital reperfusion time interval defined as the time from arrival at primary destination hospital to reperfusion intervention at the primary destination (defined as time to drug administration or balloon inflation);

• PCI transfer reperfusion time interval defined as the time from arrival at primary destination hospital and transport to a PCI capable site to the reperfusion intervention at the PCI site (defined as time to drug administration or balloon inflation).

• PCI site reperfusion time interval defined as the time from arrival at PCI site to reperfusion intervention at the PCI site (defined as time to drug administration or balloon inflation)

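### One-way ANOVA for the secondary time intervals assumes a common variance in groups defined by distance and destination; an unequal-variance method is a cheap improvement

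*Protocol article*

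**What the plan says.** The Analysis Plan of the protocol article sets the method for the intervals: "The primary outcome, and treatment time intervals, will be analyzed with one-way ANOVA and subsequent pair-wise multiple comparison procedures across the four treatment strategies". Covariates are then handled by multiple linear regression. The text names no unequal-variance form, no transformation and no rank method, and it does not name the pairwise procedure.

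The groups are set under Study Design. The split between groups 1 and 3 (far) and groups 2 and 4 (near) follows distance: "Bypass eligibility was based on transport distance of patients from their pick-up location to PCI center and the cut-off point was 60 kilometres". Destination differs as well. Groups 1, 2 and 3 go to the nearest ED; group 3, for example, is "12-lead PHECG and prehospital notification transported to the nearest receiving ED who were not eligible for bypass to a PCI center based on transport time". Only group 4 is "12-lead PHECG with prehospital notification and eligible for bypassing the nearest receiving ED with transport to a PCI center".

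Treatment Time Intervals lists six secondary intervals. They differ in how much travel they contain:

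- Scene time contains none: "Prehospital scene time interval defined as time from arrival at scene to departure from scene".
- Transport time runs to the first destination: "Transport time interval defined as time from departure from scene to arrival at destination hospital".
- The transfer interval includes the journey between hospitals: "PCI transfer reperfusion time interval defined as the time from arrival at primary destination hospital and transport to a PCI capable site".

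The sample size section sets the group size: "The recruitment goal is to enrol 100 STEMI prospective subjects per group". No mean, SD or distribution is given for any interval.

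**The concern.** Classical one-way ANOVA and its usual pairwise follow-ups test every pair against a single variance averaged over all four groups. If the groups differ in spread, that average is too small for a pair of variable groups and too large for a pair of homogeneous ones. The first pair is then tested too liberally and the second too conservatively. Ordinary linear regression makes the same assumption when it computes standard errors.

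The design gives reason to doubt equal spread. Durations are bounded below by zero and tend to vary more when they are longer. The groups are formed by geography and destination, which drive the length of any interval that contains travel or transfer. At stake is whether the pairwise significance levels and confidence intervals for these secondary outcomes mean what they say.

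**Working it through.** **The plan's own figures.** None is given for the intervals. Table 2 concerns the binary primary outcome. A two-sided 5% test with 80% power and continuity correction gives 402, 185 and 107 per arm, against 402, 185 and 106 stated. This supports reading the 0.05 as two-sided.

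**Inputs.**
- n = 100 per group (Sample Size Calculation).
- Four groups, so error df = 400 − 4 = 396.
- Tukey as an example of a pairwise procedure (assumption; none is named). The critical value is c = 3.649/√2 = 2.580, a nominal two-sided level of 0.99% per pair.
- SD ratio r, the larger group SD over the smaller (assumption; range 1 to 3).

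**Formula.** With equal n, the pooled variance is the mean of the four group variances. For a pair (i, j):

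k = √[ pooled variance / ((σᵢ² + σⱼ²)/2) ]; actual error = 2 × [1 − Φ(k·c)].

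Take a true difference that would be detected with 80% power if the pair's own variances were used. Power with the pooled variance is then 1 − Φ(k·c − c − 0.842).

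**Scenario A: groups 1 and 3 have SD r, groups 2 and 4 have SD 1.** This could fit the transfer interval. Pooled variance = (1 + r²)/2.

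At r = 2 the pooled variance is 2.5.
- 3 v 1: k = √(2.5/4) = 0.791, k·c = 2.040, error 4.1%.
- 4 v 2: k = √(2.5/1) = 1.581, k·c = 4.079, error below 0.1%. Power = 1 − Φ(4.079 − 3.422) = 1 − Φ(0.657) = 26%.

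| r | 3 v 1 error | 4 v 2 error | 4 v 2 power (80% if unpooled) |
|---|---|---|---|
| 1 | 1.0% | 1.0% | 80% |
| 1.25 | 2.0% | 0.4% | 69% |
| 1.5 | 2.8% | 0.1% | 55% |
| 2 | 4.1% | <0.1% | 26% |
| 3 | 5.5% | <0.1% | 1% |

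Power for 4 v 2 is halved at r of about 1.75.

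**Scenario B: only group 4 has SD r.** This is possible for transport time, because only group 4 passes the nearest ED. Pooled variance = (3 + r²)/4; the 4 v 2 pair variance is (1 + r²)/2.

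At r = 1.5: k = √(1.3125/1.625) = 0.899, k·c = 2.319, error 2.0%. At r = 2: k = √(1.75/2.5) = 0.837, k·c = 2.159, error 3.1%.

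| r | 3 v 1 error | 4 v 2 error | 4 v 2 power (80% if unpooled) |
|---|---|---|---|
| 1.5 | 0.3% | 2.0% | 86% |
| 2 | 0.1% | 3.1% | 90% |
| 3 | <0.1% | 4.6% | 92% |

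The liberal pair is now 4 v 2, and its apparent power rises because the test is too lenient.

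**Family-wise error** (simulation, normal data, 200,000 runs, Tukey, nominal 5%). With 100 per group it is 5.5% and 6.4% at r = 1.5 and 2 in Scenario A, and 5.6% and 6.6% in Scenario B. If the far groups had 50 each and the near groups 150 each (assumption), Scenario A gives 12% and 19%.

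**Skewed data** (lognormal, coefficient of variation 0.5 and 0.8, 20,000 runs, Scenario A). The pooled 3 v 1 error is 2.6% to 2.9% at r = 1.5 and 3.8% to 4.2% at r = 2. With separate variances, at r from 1 to 3, it stays between 0.8% and 1.1% and the 4 v 2 power stays at 79% to 80%.

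**The case against.** The strongest objection is that the document does not establish which groups are more variable. The 60 km cut-off is measured to the PCI centre, not along the route first driven, and three of the four groups go to the nearest ED. Scene time has no distance component. The two intervals that start at hospital arrival and end with treatment in that same hospital contain no travel. The symptom-onset interval includes a delay before the call in every group, which would pull any SD ratio towards 1. All of this stands. A reader might infer that the far contrast is always too liberal and that the near contrast always loses most of its power. The documents do not support that: no SDs are given, the direction reverses in Scenario B, and power is halved only from a ratio of about 1.75.

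A reader might also quote a 12% false-positive rate for 3 v 1. That is the Scenario A figure at r = 2 for unadjusted 5% tests, whereas the plan calls for multiple-comparison procedures. With Tukey and equal groups the family-wise error rises only modestly.

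Further, pooled variance and untransformed minutes are the ordinary reading of one-way ANOVA, not words in the text, and the unnamed pairwise procedure could be an unequal-variance one. This stands in part. The choice of post-hoc test may properly sit in an analysis plan not shown. But the article does name one-way ANOVA and linear regression, so the plan would have to depart from or qualify that text.

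Finally, these outcomes are secondary, and 4 v 2 does not isolate bypass, since those groups also differ in 12-lead ECG and notification. Both limit the importance of the point.

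**Conclusion.** The point holds as a cheap improvement. The stated methods ordinarily assume equal variances, and the way the groups are formed makes that doubtful for intervals containing travel or transfer. If spreads differ by a factor of 1.5 to 2, with 100 per group and Tukey, the affected pair is tested at roughly two to four times its nominal 1% level. Which pair that is depends on the interval. In Scenario A the 4 v 2 comparison also falls from 80% power to between 55% and 26%. The SD ratios and the Tukey procedure are assumptions. Family-wise error stays within about 7% at these ratios if the groups are equal in size, but could be well above that if the more variable groups are smaller. Nothing here bears on the primary outcome, which is a proportion.

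**What to change.** In the Analysis Plan, for the treatment time intervals only:

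- Replace one-way ANOVA with Welch ANOVA, and specify Games-Howell pairwise comparisons, on minutes.
- Use heteroscedasticity-robust standard errors in the adjusted linear regression. The coefficients do not change, so the 5% rule for retaining covariates is unaffected.
- Add, as supportive results, a log-scale analysis reported as geometric-mean ratios with 95% confidence intervals, and medians with interquartile ranges.
- Keep mean minutes for the cost-effectiveness analysis. The economic part of the Analysis Plan uses average time to reperfusion and cost per reduction in that interval. Making the log scale primary would therefore change the quantity being estimated.

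The cost is a few words and a negligible loss of efficiency if variances are in fact equal. In a simulation with 100 per group and equal normal variances (400,000 runs), Tukey power of 80.0% becomes 79.6% with Games-Howell.

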We have planned a prospective cohort study to compare outcomes across two different prehospital interventions (12-lead and 3-lead) and two system changes (transfer to closest hospital versus bypass closest hospital to transfer directly to a PCI capable hospital) that do not lend themselves to evaluation by a randomized controlled trial. We anticipate there will be challenges related to ethical and privacy, oversight of data guardian abstraction, timeliness of implementation, and technological advances. We hope that this evaluation may be helpful to those involved in developing and enhancing multidisciplinary systems of care including EMS services to advance local care of patients with STEMI and to inform policy decision making and evidence based budgetary decisions that ultimately will affect care across the Province.

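### Unrestricted pairwise comparison of the four groups mixes care strategy with proximity to a PCI centre in four of the six pairs

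*Protocol article*

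**What the plan says.** The Study Design section of the protocol article defines the groups as follows.

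- Group 1 covers "3-lead PHECG and transported to the nearest receiving ED who were not eligible for bypass based on transport time"
- Group 2 covers "3-lead PHECG and transported to the nearest receiving ED who were eligible for bypass based on transport time, if 12 lead PHECG was possible"
- Group 3 has 12-lead with advance notification and goes to the closest ED, being outside the bypass limit on transport time
- Group 4 covers "12-lead PHECG with prehospital notification and eligible for bypassing the nearest receiving ED with transport to a PCI center"

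The rule follows: "Bypass eligibility was based on transport distance of patients from their pick-up location to PCI center and the cut-off point was 60 kilometres". The closing paragraph of the Discussion describes the study as a comparison of "two different prehospital interventions (12-lead and 3-lead) and two system changes".

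The Analysis Plan analyses the primary outcome by one-way ANOVA and "subsequent pair-wise multiple comparison procedures across the four treatment strategies". It then brings the Table 3 covariates in through multiple linear regression as potential confounders. None of the 15 is distance or transport time to a PCI centre, or rural/urban setting. The nearest is whether the primary destination hospital has a round-the-clock catheterization laboratory. The A Priori Subgroup Analysis section lists rural vs urban setting, academic vs non-academic hospitals, and a distance comparison among sites without PCI.

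**The concern.** Eligibility band is part of each group's definition. A comparison that crosses the band therefore changes where the patient was picked up as well as, or instead of, the care given. Group 2 is plainly meant as the comparator for group 4, since its members are those "who were eligible for bypass based on transport time, if 12 lead PHECG was possible". The stated analysis does not use that structure: it treats the four groups as one unordered factor and gives all six pairs equal standing.

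The stakes lie in how the result will be used. The Abstract hopes to support adoption of the superior strategy in all communities, and the economic analysis is also built around a superior strategy. If group 4 did better than group 3, the difference could reflect bypass, proximity, or both, and the stated comparison would not tell them apart.

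**Working it through.** **Inputs.** Group definitions and the 60 km cut-off (Study Design); 100 STEMI patients per group, alpha 0.05, 80% power, and Table 2 with a baseline of 37.4% (Sample Size Calculation); Table 3 and the all-pairs wording (Analysis Plan).

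**1. Reproducing Table 2.** The two-proportion formula with pooled variance, two-sided 0.05, 80% power and continuity correction gives 402, 185 and 107 per arm for differences of 10, 15 and 20 points. Table 2 prints 402, 185 and 106, so the plan's figures are reproduced to within rounding.

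**2. What each pair contains.** Write e for the effect of 12-lead with notification, g for the near/far difference and b for the added effect of bypass. Assume that e is the same in both bands or, equivalently, that g is the same under both ECG types. Expected values are then: group 1 = a, group 2 = a + g, group 3 = a + e, group 4 = a + e + g + b.

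| Contrast | Crosses the band? | Contains |
|---|---|---|
| 3 - 1 | no | e |
| 4 - 2 | no | e + b |
| 2 - 1 | yes | g |
| 4 - 3 | yes | g + b |
| 4 - 1 | yes | e + g + b |
| 3 - 2 | yes | e - g |

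Four of the six pairs carry g. The comparison 4 vs 3 carries all of it: if g were 10 points and b zero, 4 vs 3 would show 10 points. Bypass is isolated only by (4-2)-(3-1) = (e + b) - e = b.

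**3. Can covariates remove g?** Not with Table 3, which has no such variable. Adding distance would not settle it, because under a distance rule the bands do not overlap and the model would have to extrapolate from one to the other. The catheterization-laboratory covariate is no substitute: bypass changes the destination hospital, so adjusting for it could remove part of the bypass effect.

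**4. Illustration with no strategy effect (e = b = 0).** The setting is 100 per group, 37.4% in the far groups, 5,000 simulated trials per scenario, and Bonferroni over six pairs (an assumption, as the article names no procedure). The values of g are assumed.

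| Assumed g | ANOVA rejects | Any cross-band pair significant | Any within-band pair significant |
|---|---|---|---|
| 10 points | about 37% | about 30% | about 2% |
| 20 points | about 94% | about 89% | about 2% |

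**5. Precision at 100 per group.**

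- One within-band contrast detects about 20 points at two-sided 0.05 (19.7 to 20.7) and about 22 to 23 at 0.025.
- For (4-2)-(3-1), SE = sqrt(4 × 0.374 × 0.626 / 100) = 0.0968. The detectable difference is 2.80 × 0.0968 = 0.271, about 27 points.
- With 57.4% in two of the four groups, SE = sqrt((2 × 0.374 × 0.626 + 2 × 0.574 × 0.426) / 100) = 0.0978. Power for a 20-point bypass component is then about 53%.
- For 37.4% vs 57.4% without continuity correction, power is 57.8% with Bonferroni over six pairs and 72.7% over two. Reaching 80% needs 150 and 118 per group respectively.

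**The case against.** The best defence is that all-pairs testing already includes 4 vs 2 and 3 vs 1. Splitting the 3-lead patients by hypothetical eligibility is itself control for distance at the design stage. Before covariates enter, a four-group model and a 2×2 model with interaction fit the same cell means. The article nowhere names 4 vs 3 as the bypass comparison, and ranking contrasts is often left to a statistical analysis plan. This stands to the extent that the useful contrasts can be had from the planned data. It does not rescue the stated analysis, which gives confounded and unconfounded-by-band pairs the same status and spreads the error rate over six tests.

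Several stronger readings are tempting, but the documents do not support them.

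- *The plan ignores geography.* It does not: it pre-specifies a rural/urban subgroup and a distance comparison labelled as addressing geographical bias. Neither changes the primary contrasts.
- *4 vs 2 and 3 vs 1 are fully like-for-like.* They match on eligibility band only. The Discussion describes ECG type as a feature of regions, so EMS services and hospitals may differ too. In addition, 4 vs 2 changes 12-lead, notification and bypass together.
- *2 vs 1 is pure geography.* The two groups may also differ by EMS service, hospital and mode of reperfusion, and nothing stops a group 2 patient's nearest ED from being a PCI centre.
- *Bypass will be flattered.* The primary outcome starts at the hospital door and has separate targets for PCI (90 minutes) and fibrinolysis (30 minutes). Pick-up distance does not enter that interval directly, so proximity would act through hospital type and treatment mode. Its direction cannot be read from the documents.
- *The bands can never overlap in kilometres.* That follows from the 60 km rule, but the group definitions speak of transport time and the recruitment estimate uses 60 minutes. Under a time rule kilometres could overlap, and the groups would be separated on time instead.

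**Conclusion.** The point holds as a fault in how the primary comparison is structured. By the article's own group definitions, four of six pairs confound strategy with proximity to a PCI centre, and neither the listed covariates nor the subgroups correct this. The size of the distortion is unknown, because the documents give no near/far difference. The claim that it enters 4 vs 3 in full rests on that difference being the same under 3-lead and 12-lead, and the rejection rates above are illustrations under assumed values. The within-band contrasts are better protected but not free of regional confounding. A reader might also infer that nothing may be reported from the cross-band pairs. That goes too far, since comparing four strategies is the stated aim; it is enough to mark those pairs as descriptive.

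**What to change.** 1. Analyse the primary outcome with terms for 12-lead, bypass-eligible band and their interaction.
2. Pre-specify two primary contrasts: 4 vs 2 (the bundle of 12-lead, notification and bypass, in the eligible band) and 3 vs 1 (12-lead plus notification, in the non-eligible band). State that they match on band only and may still differ by EMS region and hospital.
3. Report (4-2)-(3-1) as an exploratory estimate of the bypass component, with the assumption that the 12-lead effect is the same in both bands and with its imprecision.
4. Report 2 vs 1 as a check on geographic and regional differences, and label the cross-band pairs as descriptive and confounded by geography.
5. Reconcile transport time and 60 km (Study Design) with 60 minutes (Sample Size Calculation) as the eligibility rule.

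The cost is wording in the analysis plan, with no new data, and the primary tests fall from six to two. The downside is that the bypass-only effect will be imprecise at 100 per group and must be described as such.
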